#### Secondary outcomes: role security and therapeutic commitment

Role security and therapeutic commitment of the participating providers will be measured by the short version of the Alcohol and Alcohol Problems Perception questionnaire (SAAPPQ) [34] at three time points: at or immediately after the first introduction meeting, at the end of the 12-week implementation period, and during the end of the four-week follow-up period. All participating providers who have signed an informed consent will be asked to complete the SAAPPQ at each of the three time points. The responses will be summed within the two scales of role security and therapeutic commitment. Individual missing values for any of the items in a domain will be assigned the mean value of the remaining items of the domain before summation.

### Randomization and blinding

Randomization will take place after formal agreement of the PHCU to take part in the trial. The PHCU will be randomly allocated to one of eight groups by the European coordinating centre, using computerized randomization stratifying by country, ensuring 15 PHCUs per group (three per country). Although the PHCUs will be randomly allocated before the baseline measurement, the research team in each of the countries and the PHCU only are informed of the allocation after collection of the baseline measurement to avoid bias as a result of group allocation. For the remainder of the study period, the PHCU and investigators will not be blind to group allocation.

### Sample size

It is estimated that 56 PHCUs (seven per eight allocation groups) with a minimum of 1,000 eligible patients per month would be needed for a 80% chance of detecting an increase in screening rates from 8% to 12% (ICC = 0.029) and that 120 PHCUs (15 per eight allocation groups) would be needed for a 80% chance of detecting an increase in brief advice rates from 4% to 6% (ICC = 0.029) (alpha = 5%). As country is used as stratification criteria each country has to include a minimum of 24 PHCUs. These conservative estimates are based on published evidence of screening and advice rates [22,23].

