**Methods/design:**

In a cluster randomized factorial trial, data from Catalan, English, Netherlands, Polish, and Swedish primary healthcare units will be collected on screening and brief advice rates for hazardous and harmful alcohol consumption. The three implementation strategies will be provided separately and in combination in a total of seven intervention groups and compared with a treatment as usual control group. Screening and brief intervention activities will be measured at baseline, during 12 weeks and after six months. Process measures include health professionals’ role security and therapeutic commitment of the participating providers (SAAPPQ questionnaire). A total of 120 primary healthcare units will be included, equally distributed over the five countries. Both intention to treat and per protocol analyses are planned to determine intervention effectiveness, using random coefficient regression modelling.

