### Aim and objectives

Our aim is to study the effectiveness of training and support (T&S), financial reimbursement, and internet based brief interventions (e-BI), targeted singly or in combination to primary healthcare units, on screening and brief intervention activities, compared to treatment as usual. The following hypotheses will be tested in the study:

1. Provision of training and support to primary healthcare providers will increase use of preventive screening and brief interventions compared to a care as usual control group.

2. Financial reimbursement to primary healthcare providers as a pay-for-performance of brief alcohol interventions will increase screening and brief intervention rates compared to care as usual.

3. Providing resources, *i.e.*, offering referral possibility to an internet-based method of delivering brief intervention, will increase screening and brief intervention rates compared to care as usual.

4. The combination of training and support, financial reimbursement, and e-BI will be more effective in increasing screening and brief intervention rates compared to single-focused implementation strategies.

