### Statistical methods

Because of the hierarchical structure of the data (individual providers nested within PHCU nested within country), we will perform multilevel analyses of the screening and advice rates to examine the effect of the implementation strategies in comparison with the controls. The intention to treat analyses will include all participating providers (see above). Per protocol analyses will include only actively participating providers (see above). In all the analyses, we will use exposure to the implementation strategy as co-variate. Exposure is defined as positive if the providers meet the following criteria: financial—the PHCU received the financial reimbursement; e-BI—the provider handed out at least one referral card; and T&S—the provider attended the two face-to-face educational meetings. If these criteria will not be met, the exposure will be defined as negative.

Analyses will be performed in SAS V9.2 and based on mixed effects model (PROC GLIMMIX and PROC MIXED). We will use a random intercept model with fixed variables.

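### The 80% power matches pooled factorial main effects, but hypotheses 1–3 are worded against care as usual, where one group versus control has about 56% (screening) and 31% (brief advice)

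*Protocol article*

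**What the plan says.** All places are in the protocol article.

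- **Sample size.** The screening statement is that "56 PHCUs (seven per eight allocation groups) with a minimum of 1,000 eligible patients per month would be needed for a 80% chance"; the difference to be found there is 8% against 12%, at an ICC of 0.029. The brief advice statement is that "120 PHCUs (15 per eight allocation groups) would be needed for a 80% chance"; the difference there is 4% against 6%, at the same ICC and an alpha of 5%. The section does not say which groups are compared, or whether the 5% is two-sided.
- **Randomization and blinding.** Eight groups, "ensuring 15 PHCUs per group (three per country").
- **Aim and objectives.** Hypothesis 1 says that training and support "will increase use of preventive screening and brief interventions compared to a care as usual control group". Hypotheses 2 and 3 set reimbursement and e-BI against care as usual. Hypothesis 4 sets the triple combination against single strategies.
- **Abstract, Methods/design.** The strategies are given separately and combined "in a total of seven intervention groups and compared with a treatment as usual control group".
- **Statistical methods.** Multilevel models will "examine the effect of the implementation strategies in comparison with the controls". The model is described only as a random intercept model with fixed variables.
- **Title and Design.** The trial is called a cluster randomized factorial trial. Nowhere does the article say that the four groups with a strategy will be pooled against the four without it.

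**The concern.** A 2×2×2 factorial trial can be read in two ways. A main effect of one strategy uses all 120 units, 60 with it and 60 without. A comparison of one strategy alone with usual care uses 30 units, 15 v 15, and sets 90 aside. The two differ greatly in power, and they answer different questions: in the main-effect contrast, three of the four comparator groups receive another active strategy, so that comparator is not care as usual.

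If the 80% belongs to the first reading and the hypotheses are tested by the second, a null result for a single strategy would be taken as stronger evidence of no effect than it is. The Discussion says that the results are meant to inform policy.

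**Working it through.** **Inputs, from Sample size:** 8% v 12% and 4% v 6%; m = 1,000 per unit; ICC = 0.029; 80% power; alpha 5%. Two-sided is assumed, because it reproduces the stated totals. One-sided totals would be 42–45 and 88–94 and do not match.

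**Design effect:** 1 + (1,000 − 1) × 0.029 = 29.97.

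**1. Reproducing the stated totals**

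Patients per side before inflation: n = (1.96 + 0.84)² × [p0(1 − p0) + p1(1 − p1)] / (p1 − p0)². Units per side: n × 29.97 / 1,000.

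- Screening: p0(1 − p0) + p1(1 − p1) = 0.0736 + 0.1056 = 0.1792; n = 879; 26.3 units per side. With pooled variance and continuity correction, n = 932 and 27.9 units, so 28 v 28 = 56 = 7 × 8, the stated figure.
- Brief advice: 0.0384 + 0.0564 = 0.0948; n = 1,860; 55.8 units per side. With pooled variance and continuity correction, n = 1,962 and 58.8 units, or 117.6 in all, which rounds up to 15 × 8 = 120, that is 60 v 60.

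Both totals are therefore those of a two-arm trial spread evenly over eight groups. That is the factorial main effect.

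**2. Power by contrast**

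Power = Φ(d/SE − 1.96), with d = p1 − p0 and SE² = 29.97 × [p0(1 − p0) + p1(1 − p1)] / (1,000k) for k units per side. Example, screening at k = 15: SE² = 29.97 × 0.1792 / 15,000, SE = 0.0189, d/SE = 2.11, power = Φ(0.15) = 56%.

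| Contrast | Units | Screening 8% v 12% | Advice 4% v 6% |
|---|---|---|---|
| Main effect, 56 units | 28 v 28 | 82% | – |
| Main effect, 120 units | 60 v 60 | 99% | 83% |
| One strategy group v control, 120 units | 15 v 15 | 56% | 31% |
| One strategy group v control, 56 units | 7 v 7 | 30% | – |

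Over two-sided variants of the formula (pooled or unpooled variance, arcsine, t reference), the 15 v 15 figures range over 53–57% and 29–31%. At 15 v 15, the increases detectable with 80% power are from 8% to about 13.5% and from 4% to about 8.3%. For 80% power at 7 v 7 (screening) or 15 v 15 (advice), the ICC would have to be about 0.007.

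**3. The cluster size used for brief advice**

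Under Outcomes, the advice rate is divided by screen positives, whereas the calculation uses 1,000 patients per unit. The article does not give the number of screen positives. Assuming 10 to 40 per unit:

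- 10 per unit: design effect 1 + 9 × 0.029 = 1.26; power 29% at 60 v 60 and 11% at 15 v 15.
- 40 per unit: design effect 1 + 39 × 0.029 = 2.13; power 59% at 60 v 60 and 19% at 15 v 15.

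**4. Hypothesis 4**

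If the triple group (15 units, higher rate) is compared with the three single-strategy groups pooled (45 units, lower rate), then SE² = 29.97/1,000 × [p1(1 − p1)/15 + p0(1 − p0)/45]. On the same inputs and effect sizes, power is about 70% for screening and 40% for advice.

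**The case against.** The strongest reply is that a trial labelled factorial, with a sample size that reproduces as main effects, was meant to be analysed by main effects. Statistical methods speaks of strategies rather than seven arms, defines exposure separately for each of the three strategies, and names a model that does not exclude three factorial indicators. The exact coding of fixed effects may also lie in an analysis plan that is not shown. This stands in part: a reader might infer that the analysis will certainly use only the 15-unit control group, and the article does not establish that. It does not remove the point, because the hypotheses themselves name care as usual as the comparator, and that is not a coding detail.

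A reader might also infer that the sample size is miscalculated. It is not: 56 and 120 reproduce. The fault is a mismatch between the contrast that fits and the hypotheses as worded.

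Nor are main effects strictly the only contrast near 80%. All seven intervention groups pooled against control (15 v 105) give 78–85% for screening at 120 units. The same contrast gives 43–55% for advice and 42–54% for screening at 56 units, and no hypothesis states it.

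Finally, adjustment for baseline or use of repeated periods could raise power. The stated calculation uses neither and the article gives no correlation, so the gain is unknown. Raising m to 3,000–4,000 adds only about one percentage point.

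**Conclusion.** The point holds for hypotheses 1–3 as worded. Under the protocol's own inputs, the stated 80% fits a comparison of four groups with four (82% for screening at 28 v 28, 83% for advice at 60 v 60). One strategy group against the control group at 15 v 15 has about 56% and 31%. These figures assume a two-sided 5% test, 1,000 patients per unit, ICC 0.029 and a single unadjusted period, with no multiplicity allowance.

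It would go too far to say that no primary hypothesis has its stated power. If main effects are what is tested, the screening figure is met. Hypothesis 4 is a separate contrast for which the article states no power. The advice figures, both 83% and 31%, depend on a cluster size that does not match the outcome's denominator, and they should not be read as the trial's actual power for advice.

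**What to change.** Reconcile the abstract, Aim and objectives, Sample size and Statistical methods, by one of two routes.

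1. **Preferred.** Make the factorial main effects the primary analysis of hypotheses 1–3: three 0/1 indicators (training and support, reimbursement, e-BI) over all eight groups, with interactions reported as a check. Reword these hypotheses as with versus without the strategy. State that the 80% refers to main effects and assumes no important interaction. Report single group v control as secondary, with its own power.
2. **Alternative.** If strategy alone versus usual care is the question that matters, keep it primary and replace the 80% by about 56% (screening) and 31% (advice, subject to the recalculation below).

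On either route, recalculate brief advice with an expected number of screen positives per unit before stating any power for it, and give hypothesis 4 its own contrast and power.

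The cost is rewording and one recalculation; the number of units and the randomization do not change. The drawback of the first route is that each main effect is an average over the other strategies, so it does not directly answer what a strategy does alone against usual care.

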### Outcomes

#### Primary outcomes: screening and brief advice rates

PHCUs will be asked to screen all patients aged 18 years and over who attended the PHCU. These patients are defined as eligible patients.

Patients will be screened for hazardous and harmful alcohol consumption with AUDIT-C [32]. Screen positives, or at risk patients, are defined as those who scored ≥ 5 for men or ≥ 4 for women on AUDIT-C. Participating staff that have signed up to the study will be asked to deliver brief alcohol advice of 5 to 15 min duration to at-risk patients, with the length and format of the brief advice based on country-specific guidelines or, for Poland where national guidelines are lacking, the European guidelines developed by PHEPA [33]. Providers of PHCUs allocated to e-BI activity will be asked to refer patients to a computerized brief advice program, considered equivalent to providing brief advice. Besides counting referral rate to e-BI, actual e-BI log-in rates of patients will be collected.

Screening and brief advice will be measured at five timepoints: during the four-week baseline period, the three consecutive four-week blocks during the twelve week implementation period; and, the four-week follow-up period, which will occur during the seventh month after the end of the twelve-week implementation period using paper tally sheets, with the exception of Catalonia who will use their electronic patient records. The tally sheets include AUDIT-C scores (*i.e.*, identification of at risk patients) with additional table to indicate the type of brief advice that was delivered to the patients at risk. Gender and age of patients will be recorded as well as the name and profession of the provider.

The screening rate will be calculated as the number of completed screens divided by the total number of consultations of all patients eligible for screening (as defined above) per participating provider times 100. The brief advice rate will be calculated as the number of BIs delivered (received oral brief advice, and/or were given an advice leaflet, and/or were referred to the e-BI program, and/or were referred to another provider in or outside the practice), divided by the total number of screen positives per participating provider times 100. Information will also be collected on the number of screen negatives who received brief advice.

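### The 80% power stated for brief advice is not supported for the outcome as defined: the calculation fits about 1,000 patients per PHCU, but the rate is per screen positive

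*Protocol article*

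**What the plan says.** The Sample size section of the protocol article gives two calculations with one ICC (0.029), 80% power and alpha 5%. For an "increase in screening rates from 8% to 12"% it asks for 56 PHCUs, seven in each of the eight groups, "with a minimum of 1,000 eligible patients per month". For brief advice it says that "120 PHCUs (15 per eight allocation groups) would be needed for a 80% chance of detecting an increase in brief advice rates", the increase being from 4% to 6%. The second figure sizes the trial. No cluster size is printed for brief advice; the 1,000 stands in the screening clause and is the only one given.

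Outcomes (primary outcomes) treats every attending adult as an eligible patient. It defines the brief advice rate as brief interventions delivered "divided by the total number of screen positives per participating provider times 100". Counts are taken in four-week blocks, three of which make up the 12-week implementation period. The article does not say what share of screened patients is expected to be positive.

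**The concern.** A patient can be screen positive only after being screened, and the plan expects 8% to 12% of eligible patients to be screened. The denominator of the brief advice rate is therefore a small part of the 1,000 eligible patients. If the 120 PHCUs were sized on about 1,000 patients per PHCU, the 80% belongs to a rate with a different denominator from the one defined.

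Brief advice is a primary outcome, and its calculation, not the 56 for screening, fixes the number of PHCUs. A null result on it would be read against a power that has not been shown for that outcome.

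**Working it through.** **Inputs.** From Sample size: 8% v 12% and 4% v 6%, ICC 0.029, alpha 5%, power 80%, 1,000 eligible patients per PHCU per month, 15 PHCUs per group. From Design and Implementation strategies: a factorial with eight groups, so a main effect compares four groups with four, 60 v 60 PHCUs. Sidedness is not stated; two-sided reproduces the figures.

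**Step 1: reproduce the plan's figures.** With p̄ the mean of the two rates and d their difference:

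- n = [1.96·√(2p̄(1−p̄)) + 0.8416·√(p1(1−p1)+p2(1−p2))]² / d²
- with continuity correction: n' = (n/4)·[1+√(1+4/(n·d))]²
- design effect: DE(m) = 1 + (m−1)·0.029, so DE(1,000) = 29.971
- PHCUs per side: n'·DE(m)/m

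Screening: n = 882, n' = 932; 932 × 29.971/1,000 = 27.9, so 28 per side, 7 per group, **56** in total.

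Brief advice: n = 1,863, n' = 1,962; 1,962 × 29.971/1,000 = 58.8, so 59 per side, 15 per group, **120** in total.

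One set of inputs gives both printed figures. Without the correction, brief advice comes to 1,863 × 29.971/1,000 = 55.8 per side, 14 per group, 112 in total.

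**Step 2: how many patients per PHCU does 80% need?** Sixty PHCUs per side give an effective size of 60m/DE(m). Setting this equal to 1,863 gives m of about 303 without correction. Setting it equal to 1,962 gives about 615 with it.

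**Step 3: how many screen positives can there be?** 1,000 × 8% = 80 and 1,000 × 12% = 120 screened patients per block; over three blocks, 240 to 360. These are ceilings, reached only if every screened patient is positive. The positive share is not in the documents, so I assume 10% to 50%. At 10% screening (the middle of 8-12%) there are 100 screens per block, giving m = 10-50 per block and 30-150 over 12 weeks.

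**Step 4: power for 4% v 6%, 60 v 60, no continuity correction.** With N = 60m/DE(m), power = Φ{[d − 1.96·√(2p̄(1−p̄)/N)] / √[(p1(1−p1)+p2(1−p2))/N]}. For example, m = 80 gives DE = 3.291, N = 1,458.5 and power 69.8%.

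| Basis | m | Power |
|---|---|---|
| One block, 10% to 50% positive (assumed) | 10 to 50 | 29% to 63% |
| One block, all screened positive (ceiling) | 80 to 120 | 70% to 74% |
| 12 weeks, 10% to 50% positive (assumed) | 30 to 150 | 53% to 76% |
| 12 weeks, all screened positive (ceiling) | 240 to 360 | 79% to 81% |
| As apparently planned | 1,000 | 83% |

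The whole table takes 4% and 6% as rates per screen positive.

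**The case against.** **The cluster size for brief advice is inferred.** This is correct. A reader might infer that 120 can come only from 1,000 patients per PHCU, and that does not hold: without continuity correction, any m from 303 to 916 also gives 15 per group. The conclusion does not depend on it, since even 303 is well above the 80-120 ceiling for a block.

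**Pooling the 12 weeks might restore the power.** At the ceiling it just about does (79-81%), so the plan's own figures do not prove a shortfall over 12 weeks. But 303 positives out of 360 screened is 84% positive at 12% screening, and at 8% screening the 240 screens fall short of 303 altogether.

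**The 1,000 is a minimum.** Larger PHCUs would have more positives. To reach 303 in one block at 12% screening with every screen positive, a PHCU would need 303/0.12 = 2,525 eligible patients a month. The power claim has to stand on its printed inputs.

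**The 4% and 6% may not be rates per screen positive.** This is the strongest objection. Background puts the share of people able to benefit who are offered these interventions at under 5%, and the 4% resembles a rate of that kind. If so, pairing 4% v 6% with a small m mixes two denominators. With purely illustrative rates of 20% v 30% per screen positive and the same ICC, m = 10 already gives 95% power. This objection stands and limits what can be said about size.

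**Conclusion.** The stated 80% is not supported for brief advice as defined. The mismatch lies in the text itself: the only cluster size is a count of eligible patients, and the outcome is a rate among screen positives. Its size is conditional:

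- If 4% v 6% is per screen positive, the document-only ceilings of 70-74% (one block) and 79-81% (12 weeks) apply. The lower ranges in the table also need the assumed positivity.
- If the 4% and 6% belong to another denominator, the power for the defined outcome is unknown and could be above or below 80%.

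A reader might infer that the trial is underpowered for brief advice, with power of 29-63%. The documents do not support that as a flat statement, because they give neither the positive share nor, with certainty, the denominator of the two rates.

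A reader might also cite the low power of one group against control (15 v 15). That is about 31% even with 1,000 patients per PHCU, so it concerns which contrast was powered and not this denominator.

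**What to change.** Recompute and restate the brief advice power, giving:

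- the expected number of screen positives per PHCU over the period to be analysed, with the screening rate and positivity assumed;
- baseline and target rates on the screen-positive denominator;
- that the power refers to the 60 v 60 factorial main effect.

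Until this is done, do not quote 80% for the current definition. Keep the outcome definition: redefining the rate per eligible consultation would change what is estimated in order to suit a calculation. The cost is one recalculation and a few sentences, with no change to data collection.

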### Statistical methods

Because of the hierarchical structure of the data (individual providers nested within PHCU nested within country), we will perform multilevel analyses of the screening and advice rates to examine the effect of the implementation strategies in comparison with the controls. The intention to treat analyses will include all participating providers (see above). Per protocol analyses will include only actively participating providers (see above). In all the analyses, we will use exposure to the implementation strategy as co-variate. Exposure is defined as positive if the providers meet the following criteria: financial—the PHCU received the financial reimbursement; e-BI—the provider handed out at least one referral card; and T&S—the provider attended the two face-to-face educational meetings. If these criteria will not be met, the exposure will be defined as negative.

Analyses will be performed in SAS V9.2 and based on mixed effects model (PROC GLIMMIX and PROC MIXED). We will use a random intercept model with fixed variables.

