4.	e-BI: In addition to receiving the same package as the control group, the e-BI group will be asked to refer identified at risk patients with an e-leaflet with unique log in codes to an approved e-BI specific package, which will be country specific, or, for Poland based on the WHO e-SBI program. The website should include the following: Log-in facility to allow monitoring of the patient (*i.e.*, patient actually log-in); suitable brief screening tool with ability to calculate score and give feedback (*i.e.*, brief intervention); appropriate information on sensible drinking guidelines; information on impact of alcohol on health and wellbeing; and a drink diary facility. Furthermore, the website could offer reminder facilities for follow-up activity.
5.	T&S and financial reimbursement: The T&S and financial reimbursement group will receive the package, T&S, and the financial reimbursement as described above.
6.	T&S and e-BI: The T&S and e-BI group will receive the package, T&S as above, and will be asked to refer identified at risk patients to e-BI as above.
7.	Financial reimbursement and e-BI: The financial reimbursement and e-BI group will receive the package and will be asked to refer identified at risk patients to e-BI as above. They will be paid for screening, referral performance to e-BI, and brief advice if actually delivered, with the system of pay as above.
8.	T&S, financial reimbursement and e-BI: The T&S, financial reimbursement and e-BI group will receive the package and T&S as above. They will be asked to refer identified at risk patients to e-BI as above. They will be paid for screening, brief advice activities, and referral performance to e-BI, with the system of pay as above.

A graphical depiction of the study is depicted in Additional file 1.

An introductory meeting (first briefing) will be held in all PHCUs that agree to participate in the study, describing the study’s purpose and the four-week baseline data collection, which will follow the introductory meeting. After the baseline data collection, all PHCUs will receive a second briefing within one month, either face to face or by telephone, tailor-made to the study group to which they are allocated.

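### The analysis section fixes post-randomisation exposure as covariate in every analysis but does not commit to using the baseline rate collected before allocation is disclosed

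*Protocol article*

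**What the plan says.** Under Primary outcomes, the article makes baseline the first of five measurement periods: "Screening and brief advice will be measured at five timepoints: during the four-week baseline period". It applies to every unit. Under Implementation strategies, "An introductory meeting (first briefing) will be held in all PHCUs that agree to participate in the study", and the baseline data collection follows that meeting. Under Randomization and blinding, PHCUs are randomised before baseline, but the national research teams and the PHCUs "only are informed of the allocation after collection of the baseline measurement to avoid bias as a result of group allocation".

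Statistical methods describes a multilevel model with providers within PHCUs within countries: "we will perform multilevel analyses of the screening and advice rates to examine the effect of the implementation strategies in comparison with the controls". On covariates it says "In all the analyses, we will use exposure to the implementation strategy as co-variate". Exposure is defined by reimbursement having been received, a referral card having been handed out, or both training meetings having been attended. On the form of the model it adds "We will use a random intercept model with fixed variables", without listing those variables. The baseline rate is not mentioned in that section.

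**The concern.** The design provides a measurement of the outcome itself, taken in every PHCU before knowledge of allocation can influence it. In a cluster trial with large clusters, most of the error comes from differences between PHCUs, and the PHCU's own earlier rate is the natural predictor of those differences. The analysis section does address covariates, but the only one it commits to arises after randomisation. The pre-disclosure one has no stated role.

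Two things are at stake. One is precision where the design is thinnest: hypotheses 1 to 3 compare a strategy with care as usual and, read as one group against control, rest on 15 v 15 PHCUs. The other is chance imbalance at baseline between such small groups, since the only stated stratification factor is country. If the role of baseline stays open, it could also be settled after the data are seen.

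**Working it through.** **Inputs from the article.** Sample size section: 8% v 12% for screening, 4% v 6% for advice, ICC 0.029, at least 1,000 eligible patients per PHCU per month, alpha 5%, power 80%, 56 and 120 PHCUs. Randomization section: 15 PHCUs per group. Primary outcomes section: the advice denominator is screen positives.

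**Assumed, because the article gives no value.** The PHCU-level correlation r between the baseline and later rate; the number of screen positives per PHCU and period; two-sided testing.

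**1. The plan's own figures.** Design effect = 1 + 999 × 0.029 = 29.971. The two-proportion formula with continuity correction gives 932 patients per arm for screening and 1,962 for advice.
- Screening: 932 × 29.971 / 1,000 = 27.9, so 28 PHCUs per arm and 56 in total.
- Advice: 1,962 × 29.971 / 1,000 = 58.8, so 59 per arm and 118 in total, which is 120 when rounded up to a multiple of eight.

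Both stated figures reproduce as factorial main effects (half the PHCUs against the other half), with no term for baseline adjustment.

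**2. Share of variance between PHCUs, screening.** m × ICC / [1 + (m − 1) × ICC] = 29 / 29.971 = 0.968, about 97%.

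**3. Screening, one group v control, 15 v 15.** Standard error = √[(0.08 × 0.92 + 0.12 × 0.88) × 29.971 / 15,000] = √(0.1792 × 0.001998) = 0.0189. So z = 0.04 / 0.0189 = 2.114, and power = Φ(2.114 − 1.96) = Φ(0.154), about 56%. Adjustment multiplies variance by 1 − r², so power = Φ(2.114 / √(1 − r²) − 1.96).

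| assumed r | variance cut | power |
|---|---|---|
| 0 | 0% | 56% |
| 0.3 | 9% | Φ(0.256) = 60% |
| 0.5 | 25% | Φ(0.481) = 68% |
| 0.7 | 49% | Φ(1.000) = 84% |

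**4. Screening, main effect, 60 v 60.** z doubles to 4.228 and unadjusted power is Φ(2.268), about 99%. There is little left to gain.

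**5. Chance imbalance.** At a true rate of 8%, the baseline difference between two groups of 15 has SD √(2 × 0.0736 × 29.971 / 15,000) = 0.0171. That is 1.7 percentage points, or about ±3.4 as a 95% range, against a target effect of 4 points. How much carries into the later comparison depends on r. Stratification by country would reduce the spread to the extent that the ICC reflects country differences.

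**6. Which r is plausible, by outcome.** Take r as the reliability of the PHCU rate times an assumed period-to-period correlation of 0.5 to 0.8 in the true PHCU rates.
- Screening, m = 1,000: reliability 0.968, r of 0.48 to 0.77, variance cut of 23% to 60%.
- Advice, assuming 10 to 40 screen positives per PHCU and period: reliability 0.29 / 1.261 = 0.23 to 1.16 / 2.131 = 0.54. This gives r of 0.5 × 0.23 = 0.115 to 0.8 × 0.544 = 0.435, and a variance cut of about 1% to 19%.

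**The case against.** The strongest reply is that the article does not exclude baseline. Its fixed variables are unlisted, and an article may leave a covariate list to the full protocol or SAP. That stands against any claim that baseline is omitted and precision is lost. A reader might infer this from the naming of a single covariate, but the text supports only that no use of baseline is committed to. The point survives as more than a request for a list, because the section does fix a covariate for all analyses and chooses a post-randomisation one.

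Second, baseline is one of the five timepoints and may enter the random-intercept model as a repeated measure. Part of the gain would then already be there. A plain change contrast has relative variance 2(1 − r): 0.80 at r = 0.6 and 0.60 at r = 0.7, against 0.64 and 0.51 for covariate adjustment. A constrained baseline mean comes close to the latter. This stands and lowers the increment at such correlations. At r = 0.5 a plain change contrast has relative variance 1.0, so it recovers nothing.

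Third, a reader might carry the screening arithmetic over to advice and expect main-effect power to climb from 83% to 92% at r = 0.5 or 98% at r = 0.7. The outcome definition does not support this. With screen positives as denominator the baseline advice rate is noisy: even if true PHCU rates never changed, r could not exceed about 0.54 at 40 positives.

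Fourth, r is unsourced. That is so, and it is why a range starting at 0.3 is shown.

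**Conclusion.** The point holds in limited form. The article commits every analysis to exposure as covariate and makes no commitment to the pre-disclosure baseline rate. The benefit that is not secured concerns mainly the screening rate in single-group comparisons with control: from about 56% power to between 60% and 84% for r from 0.3 to 0.7. This is measured against an analysis that ignores baseline and assumes 1,000 patients per PHCU and period with ICC 0.029. For screening main effects the gain hardly matters, and for advice it is probably small.

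It would be wrong to infer that the sample size is faulty. The stated 56 and 120 PHCUs reproduce without baseline adjustment and do not depend on it. Conditioning on post-randomisation exposure is a separate problem that baseline adjustment would not cure; it adds no weight to the size of this point.

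**What to change.** In Statistical methods, prespecify the PHCU-level baseline rate of the same outcome as a fixed covariate in the primary models for both rates, or model baseline as a repeated measure with its mean constrained to be equal across groups. Say which of the two is meant. Keep country, the stratification factor, in the model. Use the PHCU aggregate and not the individual provider's baseline rate, because a provider without baseline screen positives has an undefined advice rate, and state a rule for any PHCU that has none.

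The data are already to be collected. The cost is a few sentences, one extra model term and the zero-denominator rule.
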